### Methods to Handle Protocol Nonadherence and Any Statistical Methods to Handle Missing Data

Prior to enrollment, comprehensive study details will be disclosed to potential participants, with written informed consent obtained from patients and their legally authorized representatives. Investigators may discontinue participation for substantial protocol deviations (eg, nonattendance at scheduled visits), initiating replacement recruitment according to the randomization sequence.

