### Sample Size

An initial retrospective review of 10 patients who underwent hysteroscopy under sufentanil-based general anesthesia resulted in a mean QoR-15 score of 129.8 (SD 4.92). Based on published literature, the minimal clinically important difference for QoR-15 is 6 [13]. We hypothesize that oliceridine will improve the postoperative QoR-15 score by this minimal clinically important difference (6 points). Sample size was calculated using PASS 15 software with the following parameters: a standard deviation of 11.5 [13], a 2-sided α of 0.05, and 90% power. The calculation indicated that 48 patients are required per group. To account for an estimated 20% attrition rate, the total sample size was set at 120 patients (60 per group).

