### Statistical Analysis

The primary analysis will be conducted on a modified intention-to-treat population, defined as all randomized participants who receive the study drug (oliceridine or sufentanil) at anesthesia induction. The per-protocol population will consist of modified intention-to-treat participants who complete the 24-hour follow-up assessment without major protocol deviations, serving as the population for supportive analyses. All participants who receive the study drug will be included in the safety analysis set.

Primary/secondary outcomes will be analyzed using SPSS software (version 27.0; IBM Corp), with continuous variables first assessed for normality via Kolmogorov-Smirnov testing; normally distributed data will be expressed as mean (SD), nonnormal data as median (IQR), and categorical variables as counts (%). Quantitative between-group comparisons will employ independent-samples *t* tests or Mann-Whitney *U* tests, while qualitative comparisons will use chi-square, continuity-corrected chi-square, or Fisher exact tests, with all tests being 2-tailed (statistical significance threshold: *P*<.05).

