### Plans to Promote Participant Retention and Complete Follow-Up

Investigators will maintain ongoing communication with the participants throughout the trial to address concerns while ensuring protocol adherence. Participant involvement may be discontinued by investigators in cases of nonadherence to scheduled visits or substantial protocol deviations, with all collected data excluded from the final analysis per intention-to-treat principles.

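### Removing, excluding and replacing dosed participants contradicts the modified intention-to-treat primary population and leaves unclear what the 120 counts

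*Protocol article*

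**What the plan says.** Four sections of the protocol article bear on this point.

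- *Methods to Handle Protocol Nonadherence and Any Statistical Methods to Handle Missing Data*: "Investigators may discontinue participation for substantial protocol deviations (eg, nonattendance at scheduled visits), initiating replacement recruitment according to the randomization sequence".
- The section on participant retention and follow-up repeats the investigators' power to discontinue and adds the consequence: "with all collected data excluded from the final analysis per intention-to-treat principles".
- *Statistical Analysis* sets the primary analysis on a "modified intention-to-treat population, defined as all randomized participants who receive the study drug (oliceridine or sufentanil) at anesthesia induction". The per-protocol set is made up of "modified intention-to-treat participants who complete the 24-hour follow-up assessment without major protocol deviations, serving as the population for supportive analyses".
- *Sample Size*: "The calculation indicated that 48 patients are required per group", and then "To account for an estimated 20% attrition rate, the total sample size was set at 120 patients (60 per group".

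The text sets no limit on replacements. It does not say whether a replacement opens the next envelope or takes over the allocation of the patient who left. The Abstract and the Recruitment Plan speak of enrolling 120.

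**The concern.** Table 1 has a single phase after surgery, follow-up within 24 hours, and that is when the primary outcome, the 24-hour QoR-15, is collected. For a patient already given study drug, a missed visit therefore largely means missing outcome data, possibly the primary outcome. Whether she misses it may depend on how well she is recovering. Recruiting someone else does not recover her score.

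If her data are also discarded, the comparison is made among patients selected after randomisation, partly by an investigator's decision and on events that treatment may affect. Randomisation no longer protects that comparison. Labelling the exclusion intention-to-treat adds to the problem, because two analysts could follow the same article and analyse different patients.

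**Working it through.** **1. The fate of one patient under each section.** Take a patient who is randomised, dosed, misses the 24-hour visit and is discontinued.

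- Statistical Analysis: she is in the primary set because she was dosed. She is outside the per-protocol set because she did not complete follow-up.
- Nonadherence and missing-data section: another patient may be recruited in her place. This alone does not remove her; the replacement is one more randomised patient.
- Retention section: all her data are left out of the final analysis.

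The first and third statements cannot both be followed. Applying the third consistently makes the primary set resemble the per-protocol set, which the article reserves for support. The removal comes from the retention section; replacement then fills the gap and makes the loss harder to see.

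**2. The attrition allowance.** Inputs from Sample Size: 48 per group and 20% attrition.

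- 48 / (1 − 0.20) = 60 per group, 120 in total. The inflation step reproduces exactly.
- Without replacement, 120 × 0.80 = 96 evaluable, or 48 per group, which is the number planned for.
- If 120 instead means retained patients, and every loss is replaced, the number randomised is 120 / (1 − d): about 126 at 5% loss, 133 at 10% and 150 at 20%. These are upper bounds, since replacement is optional.

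So replacement is a second allowance for the same loss, and the meaning of 120 changes with it.

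**3. Does the second allowance oversize the trial?** Inputs from Sample Size: difference 6, SD 11.5, two-sided α 0.05, power 90%.

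- n per group = 2 × [11.5 × (1.960 + 1.282) / 6]² = 77.2, so 78; the t-test calculation gives 79.
- The stated 48 does not follow from these inputs. This is a separate error.
- Power by t-test for 6 points: 71.6% at 48 per group and 80.9% at 60 per group.

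Even with every loss replaced, the trial stays below its stated 90%.

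**4. Possible bias from the exclusion.** Let a fraction p of each arm be excluded, and let excluded patients score D points lower than those retained. The retained mean exceeds the mean of all dosed patients by p × D, so the group difference shifts by (p in one arm − p in the other) × D. The article gives neither p by arm nor D, so the following are assumptions:

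- 20% against 10% excluded, D = 10: 0.10 × 10 = 1 point.
- 20% against 10% excluded, D = 20: 0.10 × 20 = 2 points.
- Equal exclusion and equal D in both arms: 0 points.

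Against the 6-point target, 1 to 2 points is 17% to 33%. The direction depends on which arm loses more.

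**The case against.** The strongest defence is that the Statistical Analysis section governs. Under it a replaced patient who was dosed stays in the primary set and her replacement is an extra randomised patient, so replacement alone excludes nobody. That is correct. A reader might infer from the replacement clause that the trial becomes a completers-only sample; the documents do not support this. The clause is discretionary, it is tied to substantial deviations, and only the retention section removes data. What stands is that the retention section does prescribe that removal and conflicts with the primary population.

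A reader might also infer that allowing for attrition twice biases the result or makes the trial too large. It does neither: it raises the number randomised, and the stated inputs call for 78 to 79 per group. Nor do the documents support a forecast that 150 will be randomised and 30 of them lost from the comparison. That would require every one of the expected 20% to be discontinued, replaced and excluded.

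Blinding of participants, the anesthesiologist and outcome assessors makes differential removal less likely. However, investigators as such are not on the list of blinded parties, and blinding does not stop loss that depends on recovery.

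Finally, envelopes are opened at enrolment, so some patients may leave before dosing. Replacing them is compatible with the modified intention-to-treat set. The choice of imputation model is properly left to a statistical analysis plan and is not criticised here.

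**Conclusion.** The point holds as a conflict between stated rules. Discontinuing dosed patients and excluding their data contradicts the article's own primary population and would select the analysed sample after randomisation. Replacement adds to this by obscuring the loss and leaving the meaning of 120 undefined.

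The size of any bias cannot be determined from the document. The 1 to 2 points rest wholly on the assumed 10-percentage-point difference in exclusion and the assumed deficit of 10 to 20 points, and zero is possible. The conflict itself depends on no assumption. It should be corrected before analysis, which the article expects in the first quarter of 2026.

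**What to change.** - Remove replacement of dosed participants. At most, allow it for patients randomised but never dosed, each replacement taking the next envelope.
- State that 120 counts randomised participants.
- Delete the data exclusion in the retention section and reconcile that section and the nonadherence section with Statistical Analysis. All dosed participants, including any already replaced and those who replaced them, then stay in the primary analysis as randomised.
- Still attempt the 24-hour QoR-15 in patients who miss a visit.
- Report every replacement made, by arm and with the reason.
- Handle missing 24-hour scores using data already collected, such as the preoperative QoR-15, with a sensitivity analysis for scores that are missing because recovery was poor. The detail can sit in the statistical analysis plan.

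The cost is a wording amendment and a modest amount of analysis. If enrolment has already finished, the analysis and reporting parts can still be applied. The downside is fewer complete cases and somewhat lower power: at the planned 20% loss, about 72% with 48 per group against about 81% with 60 per group if every loss were replaced, and a smaller gap if fewer are lost. The 20% allowance does not make up for the understated base sample size, which needs its own correction.

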### Plans to Promote Participant Retention and Complete Follow-Up

Investigators will maintain ongoing communication with the participants throughout the trial to address concerns while ensuring protocol adherence. Participant involvement may be discontinued by investigators in cases of nonadherence to scheduled visits or substantial protocol deviations, with all collected data excluded from the final analysis per intention-to-treat principles.

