#### Anesthesia Protocol

Upon arrival in the operating room, standard monitoring, including pulse oximetry, invasive radial arterial blood pressure, and electrocardiography will be initiated. Thirty minutes prior to induction, the attending anesthesiologist will administer intravenous penehyclidine hydrochloride (0.01 mg/kg) and ondansetron (4 mg). Anesthesia induction will begin with a slow intravenous bolus of either sufentanil or oliceridine according to group assignment. One minute later, propofol (2 mg/kg) and cisatracurium (0.15 mg/kg) will be administered. After satisfactory neuromuscular blockade is achieved, an LMA will be inserted. Mechanical ventilation will be initiated with a tidal volume of 6-8 mL/kg predicted body weight and positive end-expiratory pressure of 5 cmH₂O. Anesthesia will be maintained using a continuous infusion of propofol (4-12 mg/kg/h), with supplemental opioids administered based on hemodynamic criteria (mean arterial pressure or heart rate >20% above baseline). The propofol infusion rate will be titrated to maintain a bispectral index value between 40 and 60. Neuromuscular blockade will be maintained with intermittent boluses of cisatracurium (one-third of the induction dose). If reversal is required, neostigmine (0.02 mg/kg) and atropine (0.01 mg/kg) will be administered. After surgery, all patients will be transferred to the postanesthesia care unit.

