#### Criteria for Discontinuing or Modifying Allocated Interventions

The criteria for discontinuing are as follows: (1) severe anesthesia/surgical complications (eg, anaphylaxis, shock, cardiac arrest, malignant arrhythmias, aspiration requiring intervention, malignant hyperthermia), (2) protocol deviation in anesthesia/surgical technique, (3) withdrawal of consent, (4) anticipated difficult airway, and (5) failed LMA placement.

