### Outcomes

The primary outcome is defined as the quality of postoperative recovery at 24 hours after surgery and will be assessed using QoR-15 (score range: 0-150; higher scores indicate better recovery). Secondary efficacy endpoints are (1) hemodynamic changes during induction (mean arterial pressure/heart rate at T0 [pre-drug], T1 [pre-LMA], T2 [post-LMA immediate], T3 [5-min post-LMA]); (2) total intraoperative opioid consumption and supplemental bolus frequency; (3) proportion requiring vasoactive agents; (4) incidence of postanesthesia care unit respiratory depression (defined as respiratory rate <6 bpm, end-tidal carbon dioxide amplitude change >50 mm Hg or <30 mm Hg, or waveform loss >20 s); (5) time to extubation; (6) opioid-related adverse events within 24 hours; and (7) Visual Analog Scale pain scores at 30 minutes, 4 hours, 8 hours, and 24 hours postextubation.

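### Excluding all data of discontinued participants contradicts the plan's own modified intention-to-treat and safety sets whenever the patient has been dosed

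*Protocol article*

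**What the plan says.** Three sections of the protocol article bear on this.

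- *Statistical Analysis* sets the populations. The primary one is a modified intention-to-treat set, "defined as all randomized participants who receive the study drug (oliceridine or sufentanil) at anesthesia induction". The per-protocol set, which is supportive, consists of "modified intention-to-treat participants who complete the 24-hour follow-up assessment without major protocol deviations". For safety: "All participants who receive the study drug will be included in the safety analysis set".
- *Methods to Handle Protocol Nonadherence and Any Statistical Methods to Handle Missing Data*: "Investigators may discontinue participation for substantial protocol deviations (eg, nonattendance at scheduled visits), initiating replacement recruitment according to the randomization sequence".
- The section headed *Plans to Promote Participant Retention and Complete Follow-Up* allows discontinuation for missed visits or for "substantial protocol deviations, with all collected data excluded from the final analysis per intention-to-treat principles".

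The last two are separate rules. One gives replacement without mentioning exclusion, and the other gives exclusion without mentioning replacement. Both are permissive, both cover missed visits and substantial deviations, and neither makes an exception for patients already dosed.

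**The concern.** An analyst who follows the retention section and one who follows the analysis section would analyse different patients. The analysis section retains a dosed patient who deviates or is lost; the retention section removes everything recorded on that patient and calls the removal intention to treat. Intention to treat requires the reverse: patients are analysed as randomized, whatever happens afterwards.

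The trial asks whether oliceridine improves recovery and reduces opioid-related complications. Events after dosing may be related to the opioid. If patients can be dropped, and others recruited in their place, because of such events, the comparison is no longer fully protected by randomization. The published result could also carry an intention-to-treat label that it has not earned.

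**Working it through.** The plan gives no figure on this point, so the check is to set the rules side by side for each kind of patient.

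| Patient | Statistical Analysis section | Retention section | Conflict |
|---|---|---|---|
| Leaves before the study opioid | Outside the modified intention-to-treat and safety sets | Data excluded | None |
| Dosed, misses the 24-hour assessment | In both sets; out of per-protocol only | All data excluded | Yes: secondary and safety data |
| Dosed, deviates, has a 24-hour QoR-15 score | In both sets; out of per-protocol only if the deviation is major | All data excluded | Yes: primary, secondary and safety data |

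**Second row.** Table 1 has one period after surgery, follow-up within 24 hours, so a patient who misses it has normally been dosed. By then the trial may already hold induction hemodynamics, "incidence of postanesthesia care unit respiratory depression", time to extubation, early pain scores and any adverse events noted. All of these would go. The primary test would not change: without a QoR-15 score the patient contributes nothing to a t test or Mann-Whitney test on observed values, whether formally excluded or not.

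**Third row.** Here a score exists and is removed. The difference between arms of 60 shifts by d × (k1 − k2)/60. Here d is the average deficit of the removed patients against those kept, and k1 and k2 are the numbers removed in each arm. The documents give none of these, so the following are assumptions that show only how the formula behaves:

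- k1 = k2 with the same d: shift 0.
- d = 10, one more patient in one arm: 10 × 1/60 = 0.17 points.
- d = 30, two more: 30 × 2/60 = 1.00 point, or 1.00/6 = 17% of the 6-point target. The standard error is 11.5 × √(2/60) = 2.10, so this is 1.00/2.10 = 0.48 standard errors.
- d = 12, with 5% removed in one arm and 10% to 20% in the other: 12 × 0.05 = 0.6 to 12 × 0.15 = 1.8 points.

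**Safety.** If one dosed patient with an event is replaced by a typical patient, that arm's incidence p falls by (1 − p)/60: 1.50 percentage points at p = 10%, 1.17 at 30% and 0.83 at 50%. These values of p are assumptions too.

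**Replacement.** The Sample Size section already allows for losses: 60 × 0.80 = 48 per group. By the plan's own scheme, replacement comes on top of that allowance.

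**The case against.** **The analysis section should govern.** It defines all three sets explicitly, whereas the exclusion is one permissive sentence in a section on retention and may be a slip. That is a fair reading of intent, and nothing shows that the rule has been used. But both statements stand in the current text, and an unseen analysis plan would not remove the contradiction from the protocol. If it is a slip, it is quickly corrected.

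**The primary result is safe.** For the protocol's own example, missed visits, this holds. A reader might infer that dropping non-attenders biases the QoR-15 comparison; the documents do not support that, because such patients have no 24-hour score. The risk to the primary outcome is confined to deviators who do have one.

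**Blinding prevents selection.** In part. *Randomization and Blinding* names participants, their representatives, the anesthesiologist and the outcome assessors. It does not name the investigators who decide on discontinuation. Blinding also does not stop selection on events that the drug itself may cause.

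**The stopping criteria go further still.** A reader might infer that the list in *Criteria for Discontinuing or Modifying Allocated Interventions*, which includes "2) protocol deviation in anesthesia/surgical technique, (3) withdrawal of consent, (4) anticipated difficult airway, and (5) failed LMA placement", also triggers exclusion and replacement. It is true that failed placement comes after dosing, since the opioid opens induction and only later is it said that "After satisfactory neuromuscular blockade is achieved, an LMA will be inserted". But that section's heading limits it to the intervention, and it contains no exclusion or replacement rule. The shared term for deviations is not enough to join it to the later sections. Its silence on continued follow-up is detail that a condensed article may leave to the full protocol.

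**Conclusion.** The contradiction is real and rests on the text alone: a dosed patient to whom the discontinuation rule is applied cannot be both retained under the analysis section and excluded under the retention section. The intention-to-treat label on the exclusion is wrong.

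The consequence depends on the case. With a missed 24-hour assessment, secondary and safety data are lost. With a deviation and a recorded QoR-15 score, the primary comparison is also selected on a post-randomization event at the investigator's discretion.

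The size is unknown. The scenarios above run from 0 to 1.8 QoR-15 points, but every deficit, count and incidence in them is assumed, so they neither show a bias in this trial nor show that it would be small. The text should be corrected before analysis; the documents do not support calling the trial's result biased.

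**What to change.** In the nonadherence and retention sections:

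1. Delete the exclusion of collected data, the intention-to-treat phrase attached to it, and replacement of dosed participants.
2. State that all data of dosed participants stay in the modified intention-to-treat and safety sets, and that deviators and non-completers leave the per-protocol set only.
3. State that the 24-hour QoR-15 and adverse events are still obtained where possible, unless consent to data collection is withdrawn.
4. If a dosed patient has already been excluded, restore the data before analysis and keep any replacement as an additional randomized patient. Enrollment began in July 2025 and analysis is expected in the first quarter of 2026, so this should be checked before analysis begins.

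The section on discontinuing or modifying allocated interventions needs no change.

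The cost is a few sentences, since the 24-hour assessment already exists. There are two downsides. Some scores will reflect care outside the protocol and may slightly dilute the contrast. A dosed patient without a QoR-15 score, although kept in the set, still adds nothing to an observed-case primary test, so retention does not make up for every loss. Whether 48 evaluable patients per group are enough is a separate question on which this fix does not depend.

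### The retention section removes all data of participants discontinued for missed visits or substantial deviations and calls this intention-to-treat, contradicting the protocol's own modified intention-to-treat and safety sets

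*Protocol article*

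**What the plan says.** Three sections of the protocol article's Methods bear on this.

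- **Statistical Analysis.** The primary population is a modified ITT set, "defined as all randomized participants who receive the study drug (oliceridine or sufentanil) at anesthesia induction". For safety: "All participants who receive the study drug will be included in the safety analysis set". Neither definition makes an exception for deviation or discontinuation. The per-protocol set is the only one that does: its members must "complete the 24-hour follow-up assessment without major protocol deviations, serving as the population for supportive analyses".
- **Plans to Promote Participant Retention and Complete Follow-Up.** "Participant involvement may be discontinued by investigators in cases of nonadherence to scheduled visits or substantial protocol deviations", and this happens "with all collected data excluded from the final analysis per intention-to-treat principles".
- **Methods to Handle Protocol Nonadherence and Any Statistical Methods to Handle Missing Data.** Investigators may discontinue participation for substantial deviations, with non-attendance as the example, "initiating replacement recruitment according to the randomization sequence".

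A fourth section, Criteria for Discontinuing or Modifying Allocated Interventions, lists "protocol deviation in anesthesia/surgical technique" among its grounds. It contains no rule about data.

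**The concern.** The retention clause takes out of the analysis people whom the statistical section puts in. It also gives as its reason the principle that would keep them. Dropping participants because of what happened after randomization is a per-protocol type of exclusion.

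Two things are at stake:

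- **The primary comparison.** Discontinuation is at the investigators' discretion and comes after allocation. A deviation in technique can follow the study drug and be a consequence of it. If such exclusions differ between arms and those excluded recover differently, the groups compared are no longer the groups randomized.
- **Adverse events.** These are a secondary outcome and part of the stated aim. The clause covers all collected data and makes no exception for safety records, so events in exposed patients could drop out with the rest.

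The replacement rule adds to the problem, because together the two sections describe removing a participant and recruiting another in that place. Two incompatible definitions also leave the choice of primary population open until after results are known.

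**Working it through.** **1. The rules side by side, for participants who received study drug at induction.**

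| Participant | Statistical Analysis section | Retention section, if discontinued |
|---|---|---|
| Substantial deviation, 24-hour QoR-15 available | In modified ITT and safety sets; out of per-protocol if the deviation is major | All data out |
| Missed 24-hour assessment | In modified ITT and safety sets; out of per-protocol | All data out |

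In both rows one section includes the participant and the other removes the participant. Anyone discontinued before dosing is outside the modified ITT and safety sets under either rule, so the conflict is confined to dosed participants.

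**2. Which of these affect the primary endpoint.** A participant with no 24-hour QoR-15 contributes nothing to the stated *t* test or Mann-Whitney test, whether or not the retention clause is applied. For the primary endpoint the clause therefore matters mainly in the first row. In the second row it still removes intraoperative, recovery-room and adverse-event data.

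**3. The plan's own loss figure.** The Sample Size section inflates 48 per group for 20% attrition: 48 / (1 − 0.20) = 60 per group, which reproduces. That is an allowance for attrition in general. The protocol gives no rate at which investigators discontinue dosed participants, so the exclusion rates below are assumptions.

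**4. Size of a possible shift.** Let f₁ and f₀ be the shares excluded in the two arms. Let D be the mean QoR-15 deficit of excluded against retained participants, taken as equal in both arms. An arm's retained mean exceeds its full mean by f × D, so

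shift in the estimated difference = (f₁ − f₀) × D.

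| Assumed exclusion (of 60 per arm) | Assumed D | Shift | Share of the 6-point target |
|---|---|---|---|
| 10% v 5% (6 v 3 patients) | 10 | 0.05 × 10 = 0.5 | 0.5 / 6 = 8% |
| 20% v 10% (12 v 6 patients) | 20 | 0.10 × 20 = 2.0 | 2.0 / 6 = 33% |
| 20% v 20% | any | 0 | 0% |

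The shift favours whichever arm loses more of its poorly recovering patients, so it can go either way.

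**5. Effect on type I error.** Take the plan's SD of 11.5 and, as an approximation, 48 analysed per group. The standard error is 11.5 × √(2/48) = 2.35. With no true effect, the two-sided rejection probability is 1 − Φ(1.96 − shift/2.35) + Φ(−1.96 − shift/2.35). A shift of 0.5 gives 5.5%, a shift of 2.0 gives 13.6%, and no shift gives 5.0%.

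**The case against.** The best defence is that the retention clause is a drafting slip. The statistical section defines its sets explicitly, and a reader could expect it to prevail over one clause under a retention heading. That is plausible, but the protocol does not say which governs. The replacement rule points the same way as the clause, and the clause is unqualified.

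Blinding also counts against a large effect. The Randomization and Blinding section keeps participants, the anesthesiologist and outcome assessors unaware of allocation, which limits selective discontinuation by arm. It does not stop a drug effect from causing a deviation, and the list of blinded roles does not expressly include the investigators who decide on discontinuation.

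Some stronger readings are tempting, and the document does not support them:

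- **Patients with severe complications or failed laryngeal mask placement are deleted.** These are grounds for stopping the intervention, in a section with no data rule. The retention clause names only missed visits and substantial deviations; of the stopping grounds, only a deviation in technique clearly overlaps.
- **Serious adverse events will be lost from the safety set.** This would need serious events to trigger the clause, and the clause to override the specific sentence defining the safety set. Neither is established. Loss by way of a deviation is possible.
- **About 20% of patients, 24 of 120, will be excluded this way.** That treats the attrition allowance as an investigator-exclusion rate and ignores that patients without a score drop out of the test anyway.
- **The result is biased.** Bias needs exclusions that differ by arm and relate to outcome, or score gaps that differ between arms. The protocol has no data on either.

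**Conclusion.** The contradiction stands on the text of the protocol article alone; it is not a detail that a separate analysis plan could be presumed to supply. The retention clause, the replacement rule and the population definitions cannot all be followed for dosed participants, and the label intention-to-treat is wrong for what the clause does. Following the clause as written would turn the primary analysis into a per-protocol type of analysis.

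The consequence is a possible bias of unknown size. The 0.5 to 2 points rest on assumed exclusion rates and deficits with no source in the protocol, and the upper end, with a 20-point deficit (20 / 11.5 = 1.7 planning SDs), is a severe case. Zero is also within the range. The correction is needed because the conflict decides who is in the primary and safety analyses, and it should be made before anyone can see which choice favours which arm.

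**What to change.** **Retention section.** Replace the exclusion clause with text to this effect:

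> All data collected from participants who received study drug are retained, including data from those discontinued or with protocol deviations. These participants are analysed in the group to which they were randomized in the modified intention-to-treat population, and are included in the safety set. The 24-hour QoR-15 and adverse events are still collected after discontinuation unless consent for follow-up is withdrawn. Protocol deviations lead to exclusion only from the supportive per-protocol analysis.

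**Nonadherence and missing data section.** State that any replacement participant is additional and does not displace the randomized participant. Correcting the retention clause alone would leave this rule in conflict.

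**Data already handled under the clause.** Restore the collected data of any dosed participant removed so far, before unblinding. The Results section reports first enrolment on July 11, 2025, 55 participants by September 2025, and analysis in the first quarter of 2026, so this cannot wait.

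**Cost.** A short amendment and some data handling. The 24-hour assessment is already scheduled, so no new procedure is needed. Follow-up that was not collected for participants already discontinued cannot be recovered, and the report should say how many there were in each arm.
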